## Methods

2

### Study design

2.1

The study will employ a within-subjects, randomized crossover design. Participants will be paired (i.e., matched pairs) by the head coach according to registered gender and athletic level. After the familiarization, each matched pair will be randomly assigned in a counterbalanced manner to either commence with the experimental condition (EXP) or the control condition (CON) first. A pre- (T0) and post-test battery (T2) will be conducted for the two conditions (see Fig. 1). Additionally, immediately before VR combat (VC) and traditional one-on-one combat (TC) in the specialized warm-up, the subjective perceptions will be checked again (T1) for standardization.

**Fig. 1 fig1:**
[figure not shown]
The flow chart and timeline of the study design. EXP, experimental condition; CON, control condition; VC, virtual reality combat; TC, traditional one-on-one combat; MVAS, subjective mental fatigue; RPE, subjective physical fatigue; VAS-Re, readiness to perform; VAS-Enj, enjoyment; PVT-B, brief psychomotor vigilance test; FST, fencing-specific test; NASA-TLX, NASA task load index; HR, heart rate; T, test battery.

### Ethics and trial status

2.2

The study has been approved by the ethics committee of Tsinghua University (THU-01-2026-0021). The study is registered in Open Science Framework (10.17605/OSF.IO/7YCZU) and will be operated following the SPeCIFY guidelines [23].

### Participants

2.3

To address the primary purpose, the sample size has been calculated via G∗Power 3.1 based on the intended time and condition interaction effect. In a previous study, Harris et al. (2020) used a similar design to compare the training effect in a VR environment with the real-world environment on motor skill performance [24]. They reported a significant, partial eta squared = 0.12 interaction effect. Extracting the effect size value, which corresponds to a Cohen's f = 0.369, with α = 0.05, power (1−β) = 0.90, correlation among repeated measures = 0.5, and non-sphericity correction ε = 1, the minimum required sample size has been determined to be 15. Due to the practical constraints in athletes' recruitment, combined with the possible dropouts (>15%) and the counterbalanced consideration for matched pairs, 20 participants will be recruited to address the first hypothesis.

Active, senior Epee fencers from a university fencing club, featuring a Tier 2–3 (i.e., a trained to well-trained) profile [25], will be considered and screened for eligibility. Eligible participants will receive an email/paper file with an official invitation and informed consent. However, the actual purposes will be masked (i.e., single-blind) by the experience of new VR devices and the internal performance tests in scheduled training sessions. Unblinding procedures will be conducted after completion of data analysis. Following completion of informed consent, online questionnaires will be sent to collect demographic, health, fencing, and lifestyle information. The information will be recorded for further eligibility screening (detailed criteria are seen in Table 1). Participants retain the right to stop participation in the study at any moment.

**Table 1 tbl1:** The detailed inclusion and exclusion criteria for eligibility.

	Inclusion criteria	Exclusion criteria
1	Aged 18–35 years	Concurrently taking the role of assistant coach/trainer
2	Active Epee fencers from the university club	Training as a Sabre or Foil fencer
3	Being enrolled as a university student	High myopia (no glasses) and red/green color vision defects
4	Understanding concepts both in Chinese and English	Having sleep disorders
5	Being able to provide informed consent individually	Taking any medical treatment during the study
6	Training ∼3 times per week for a competitive purpose	Taking any academic course/examination before tests
7	At least local-level representation in Epee	Having official competitions during the study
8	At least 12 months free from physical injury	Habitual smoker
9	No history of mental illness	Caffeine intake less than 2 h before tests

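### The 90% power claim for 15 fencers is unsupported, because a published partial eta squared was entered as a raw-scale effect size; what 20 fencers deliver depends on a source design the protocol does not describe

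*Protocol article*

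**What the plan says.** Section 2.3 (Participants) says the calculation was done in G*Power and was "based on the intended time and condition interaction effect". The effect size comes from an earlier comparison of virtual-reality with real-world training, which the protocol describes as having a design like this one: "They reported a significant, partial eta squared = 0.12 interaction effect". This is converted to f, "which corresponds to a Cohen's f = 0.369", and entered "with α = 0.05, power (1−β) = 0.90, correlation among repeated measures = 0.5" and "non-sphericity correction ε = 1". The result is that "the minimum required sample size has been determined to be 15". After allowing for recruitment constraints, dropout above 15% and the pairing, "20 participants will be recruited to address the first hypothesis".

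The section does not state the number of groups, the number of measurements or the effect-size option chosen in the software. It gives no sample size, degrees of freedom or allocation for the source study.

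Section 2.1 makes the trial a within-subject crossover with the test battery at T0 and T2 in each of two conditions. Section 2.11 fits time, condition and their interaction as fixed effects with a random intercept per fencer. Section 2.9.1 collects MVAS and RPE at T0, T1 and T2.

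**The concern.** For RT, RAcc, LT and LAcc, the interaction in a 2 (time) by 2 (condition) within-fencer layout is a single contrast: the change under virtual combat minus the change under traditional combat. It has 1 df. A minimum of 15 should come from a calculation for that contrast, with the effect size on the scale the formula expects.

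Two things looked wrong. The figure of 15 seems to belong to a test with more degrees of freedom than the interaction has. And f was derived from a published partial eta squared but combined with a correlation among repeated measures, as though it were a raw-scale f that still needed adjusting for within-person correlation. The second error inflates power.

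This calculation is the only justification given for the sample size behind the first hypothesis. A 90% figure that the design may not have would give a non-significant interaction more weight than it deserves.

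**Working it through.** **Inputs (section 2.3).** Partial eta squared 0.12; alpha 0.05; power 0.90; correlation rho = 0.5; epsilon = 1; stated minimum 15; planned N = 20; dropout above 15%, so at most 0.85 × 20 = 17 completers.

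**1. Reproduce f.** f² = 0.12/0.88 = 0.1364, so f = 0.369. This agrees.

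**2. Reproduce N = 15.** The default repeated-measures F test with one group has lambda = f² × N × m/(1 − rho), with df m − 1 and (N − 1)(m − 1). The first N reaching 90% power is:

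| Measurements m | N |
|---|---|
| 2 | 22 |
| 3 | 18 |
| 4 | 15 |
| 5 | 13 |
| 6 | 12 |

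With m = 4, power is 0.892 at N = 14 and 0.915 at N = 15. Two groups with m = 4 also give 15. So 15 points to four measurements in one repeated factor, with 3 numerator df. This setting is inferred; the protocol does not state it.

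**3. Effect of the scale.** With m = 4 and rho = 0.5, f²N is multiplied by 4/(1 − 0.5) = 8. At N = 15, lambda = 8 × 0.1364 × 15 = 16.4. On a 1-df within-person contrast, a noncentrality of 8f²N corresponds to a partial eta squared of 8f²/(1 + 8f²) = 1.091/2.091 = 0.52, not 0.12.

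**4. Which error costs the power.** Suppose f = 0.369 really were a raw-scale value with rho = 0.5. The 1-df contrast would then have dz = 2f/√(1 − rho) = 0.739/0.707 = 1.04, with power of 96% at N = 15 and 99% at N = 20. Correcting the factor alone therefore raises power. Keeping 3 df but treating 0.12 as a partial eta squared, lambda = f² × 3(N − 1), gives 61% at N = 20, and 90% needs 37. The loss comes from the effect-size entry.

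**5. Scenario A: 0.12 is a within-subject 1-df effect.** Here lambda = f²(N − 1) or f²N, with df 1 and N − 1.

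| N | Power |
|---|---|
| 15 | 25–27% |
| 17 | 28–30% |
| 20 | 33–35% |

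About 60 fencers give 80% and about 80 give 90%.

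**6. Scenario B: 0.12 came from two groups compared on change scores.** The between-group effect on change is d = 2f = 0.739. In a crossover, dz = d/√(2(1 − r)), where r is the correlation between a fencer's two change scores. The protocol does not give r, so it is an assumption here.

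| r | dz | Power at N = 20 |
|---|---|---|
| 0 | 0.52 | 60% |
| 0.25 | 0.60 | 73% |
| 0.5 | 0.74 | 88% |
| 0.7 | 0.95 | 98% |

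**7. MVAS and RPE.** If all three time points are modelled, the interaction has 2 df. At partial eta squared 0.12 and N = 20, power is about 49% with lambda = f² × df2 and 28% with lambda = f²N.

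**8. What 20 fencers detect.** For the 1-df contrast at two-sided 0.05, dz is about 0.66 for 80% power and about 0.76 for 90%. Scenario A corresponds to dz = √0.1364 = 0.37.

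**The case against.** The strongest reply is that the low figure depends on a source the protocol barely describes. Calling its design similar does not establish that 0.12 is a within-subject 1-df effect. Under a two-group source with well-correlated change scores, 20 fencers could have close to 90% power or more. This stands. A reader might infer that the trial simply has a one-in-three chance of success; the documents support that only as one conditional scenario. Scenario B does not rescue the stated claim, though: the correlation of 0.5 was entered for repeated measures, not for paired change scores, and nothing is offered for the latter.

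A second reply is that the four-level setting is inferred and is not what lowers the power. Both parts are right. Its relevance is that 15 does not come from a 1-df test of the interaction.

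A third concerns a tempting shortcut: an observed 0.12 with 20 fencers gives F(1,19) = 0.1364 × 19 = 2.59, p = 0.12, so the planned effect could not reach significance even if seen. That does not fit the planned model. A random-intercept model with four observations per fencer tests the interaction on about 19 × 3 = 57 df, where 0.12 gives F = 0.1364 × 57 = 7.8, p = 0.007. With Scenario A's noncentrality, power on 57 df is still only about 35–37%, so the main point survives.

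Finally, the protocol contains no rule that a null result will be read as equivalence. That is a risk of interpretation, not something the plan says. The dropout allowance is also sound: 15/0.85 rounds up to 18, below 20.

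**Conclusion.** The statement that 15 fencers give 90% power for the time-by-condition interaction is not supported and should not stand. It is reproduced only by a 3-df test that is not the performance interaction, with a published partial eta squared treated as a raw-scale effect and its noncentrality inflated eightfold. That the effect was misentered is firm, given the protocol's own inputs. The size of the shortfall is conditional. It is large (33–35% at 20 fencers, 28–30% at 17 completers) if the source effect was a within-subject 1-df interaction, which is the reading the protocol's description suggests. It ranges from substantial to none (60% to 98% at 20) if the source compared two groups. For MVAS and RPE the interaction may have 2 df, which the calculation does not address.

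**What to change.** In section 2.3, keep 20 fencers and justify the number by feasibility, which the section already invokes. Delete the claim that 15 gives 90% power. In its place, state that for the 1-df difference in change between conditions, at two-sided 0.05, 20 fencers give 80% power for dz of about 0.66 and 90% for dz of about 0.76.

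If power for a partial eta squared of 0.12 is still quoted, give the source study's design and degrees of freedom and present the figure as conditional: about 33–35% for a within-subject 1-df source, or about 60% to 98% for a two-group source as the change-score correlation goes from 0 to 0.7. Say whether T1 enters the MVAS and RPE models, since that decides whether the 1-df statement covers them. Add that a non-significant interaction will be interpreted from its confidence interval.

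The cost is wording only, with no extra participants and no design change. The downside is that the stated power becomes less favourable.

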### Procedures

2.4

Eligible fencers visit the club pistes 3 times at a fixed slot (e.g., weekly routine training session at 15:00–17:30 to improve adherence), including a familiarization and two conditions (EXP/CON). The washout period will be at least 48h between conditions. The EXP and CON will take approximately 50min. Upon arrival and after preparation, a 15-min standardized general warm-up will be organized by the physical coach before T0. Next, 10min technical drills will be provided by the head coach. In EXP, the two fencers will start VC on their own for 10min. In CON, the paired fencers will conduct TC in the same format for 10min. Immediately before and after the 20-min specialized warm-up (i.e., technical drills and VC/TC), standardized measurements at T0 and T2 will be performed as follows: a 1-min digital questionnaire to collect subjective perceptions, a brief psychomotor vigilance test (PVT-B) to evaluate the reaction performance for 3min, and an Epee fencing-specific test (FST) to assess the reaction speed and lunge attack accuracy of the random targets for another 3min. Between the technical drills and VC/TC (T1), the questionnaire will be prompted to the fencers. Participants will be equipped with HR chest bands (Firstbeat, Garmin, Finland) throughout conditions to check the physiological response to VC/TC.

### Field setting

2.5

The study will be performed at Tsinghua University's fencing club (Haidian District, Beijing, China) within a controlled training environment. Three fencing pistes will be prepared as shown in Fig. 2. Two half-pistes (7m) with two fencer-shaped dummies will be set for two FSTs in mirrored layouts. The third piste will be prepared for warm-ups. Particularly, the paired fencers will conduct the 10-min VC separately at each end of the piste (14m).

**Fig. 2 fig2:**
[figure not shown]
The fencing piste settings and the general fencing club layout.

### Familiarization

2.6

During the first visit, participants will receive tutorials on wearing VR headsets and HR chest bands properly, as well as manipulating VR controllers to combat. They will be fully familiarized with the related concepts and the entire test battery. The test feedback will be provided for timely guidance and more repeats, if necessary. Particularly, the mental fatigue definition will be given based on Russell et al. (2019) across elite sports contexts [26] and Bian et al. (2025) among Chinese fencers [6], with specific examples of official elimination bouts, examinations, long-distance driving, and prolonged social-media use as the potential inducers.

### Generalized warm-up section

2.7

The structured 15-min physical warm-up is commonly applied in the club's collective training. This will be executed by the matched-paired fencers together. The light aerobic nature consists of a 2-min jogging, a 3-min shuttle run, a 5-min dynamic stretching, and 5-min physical drills, including stepping, hopping, jumping, side-sliding, agility movements, and throwing the medicine ball against the wall. Immediately after the section, the participants will dress in their fencing clothes.

### Specialized warm-up section

2.8

#### Virtual reality combat

2.8.1

Two VR headsets (Quest 3, Meta, US) with the same fencing-themed exergames named "Fencing VR: En Garde Arena" (Abstron Pvt Ltd., Pakistan) will be prepared. One VR headset will be equipped with two controllers (held with both hands) for each of the two fencers (see Fig. 3 A and B). The combat area (i.e., piste) will be framed consistently by the researcher. The Epee competition mode and its virtual environment will be selected for standardization. The VC mirrors the official rules and core cognitive demands of real Epee combat, without any physical impact from the avatar and virtual sword. Participants will compete (against VR as in Fig. 3 C and D) individually for 10min, during which the mean value of the HR response (HRmean) will be calculated.

**Fig. 3 fig3:**
[figure not shown]
Virtual reality combat. A, participant in the virtual reality combat; B, the virtual reality headsets and controllers; C, the first perspective of the exergame interface; D, the moment the participant engages in combat against the avatar.

#### Traditional one-on-one combat

2.8.2

In official competition, pre-competition preparation after the physical activation typically follows a specialized warm-up section including coach-led technical drills (i.e., footwork, distance, lunge, blade exercises) and a phase of one-on-one combat. This simulation involves high-intensity engagements where fencers execute actual sword fighting. In TC, the paired fencers will be asked to maintain the official attacking tempo to score point by point against each other for 10min, as VC, following the FIE (Fédération Internationale d'Escrime) competition rules. The combat will be controlled under strict timing via an electronic scoring apparatus, which is commonly used in daily training and competitions. The HRmean in TC will also be calculated.

### Test battery

2.9

#### Questionnaire

2.9.1

The digital questionnaires will be activated and presented on the tablet at each measurement (i.e., T0, T1, T2). The survey platform (www.wjx.cn) will record the sequence, starting and finishing time automatically. The questions will be answered by reading and sliding the digital scales. The VAS has been validated for fatigue assessments and applied during the real fencing training sessions and competitions for the subjective mental fatigue measures (MVAS) [8]. The participants will slide the marker of the electronic scale to answer "How mentally fatigued do you feel right now?" at T0, T1, and T2. The marker will be initially positioned at "0″ and hidden until participants touch the interface. Two ends of the line will be anchored from "0″ to "100″, indicating "not at all" and "maximum" levels of mental fatigue, respectively. The backend of the online system will record the MVAS by converting it into a 0–100 AU digital form. The digital scale will allow a reset and require confirmation before submission to ensure the value is aligned with the intended response. Meanwhile, after each MVAS measure at T0, T1, and T2, the Rating of Perceived Exertion (RPE) will be measured via the digital CR-10 for subjective physical fatigue [27]. Similarly, at T2, the participants will be further asked to report "readiness to perform" (VAS-Re) and "enjoyment" (VAS-Enj) on VAS following the single-item approach [28], and NASA-TLX (6 subscales on a 21-point Likert scale) based on their experience with the specialized warm-up section. The total estimated completion time for all questionnaires is 1min.

#### Brief psychomotor vigilance test

2.9.2

The PVT-B has been validated for the reaction performance under a fatigued state and built as a compatible smartphone application [29]. The application (i.e., PVT Research Tool, US) has been utilized for mental fatigue tracking as the behavioral indicators during the real fencing training and competition [8]. Participants will be instructed to gaze at a grey cross on the black screen center and touch the screen as soon as the red, solid circular stimulus appears. They will be required to keep the RT as short as possible, but not to touch the stimulus too soon (i.e., false start or anticipation, display a "Too fast, please wait for the red circle" warning when the RT < 100 ms), or too slow (i.e., timeout, display "time expired" warning when the RT > 10000 ms). The inter-stimulus intervals will vary randomly from 1000 to 4000 ms. After completion, the background system will file each trial's outcomes with the date, starting time, and exact time of every touch. The average RT of the valid touches, the number of valid responses, and false starts will be recorded. Furthermore, the number of lapses (i.e., errors of omission, RT threshold ≥355 ms) defined by Basner et al. [29] will also be applied. For the reaction performance, the accuracy score (RAcc) will be calculated as the ratio of the touches from 100 to 354 ms among all touches. This study will compare the RT and RAcc as behavioral indicators of mental fatigue [8] before and after the specialized warm-up section.

#### Epee fencing-specific test

2.9.3

The study follows the test settings and instructions from Varesco et al. [4]. The FST consists of three shuttles (forward and backward) over 2m for men and 1.75m for women Epee fencers. This adjustment for the women's group has been deemed necessary based on the height difference. Shuttles must be completed within 9s. Participants will be taught to focus their attention on the eight flash-impact sensors (ReactionX Pro, China) attached to a fencer-shaped dummy (2 × 1m), as presented in Fig. 4. After the 9s shuttling, a green-colored sensor will be shown as the random lunge attack target. The target will undergo a randomization with replacement, that is, the same one could be presented multiple times. Once the target is presented, participants will be instructed to execute a lunge to deliver a valid hit on the middle of the sensor (i.e., a final attack to score) via the sword tip as quickly as possible. Furthermore, to better simulate the possible correction and reaction inhibition in real fencing, an incongruent cue will be presented in 10% of the trials [4]: a sensor will be flashed in red color for 300 ms before the real green target is shown. The incongruent cue will be presented close to the real target (i.e., within 40 cm) to mimic the real-world fast displacement in fencing. The trial will be separated by 9s for passive rest to simulate the temporal demands (i.e., work-to-rest ratio of 1:1) in Epee. Thus, each trial will last 18s. One FST will include 10 trials for 3min. The test outcomes will be the number of lunges hits on the real targets, hits on the wrong target, misses the targets, and the time from the moment each target is activated (i.e., lights up) to the moment it is hit or missed. Then, the average value of the lunge reaction time (LT) of the valid hits and the lunge attack accuracy (LAcc) will be calculated for analysis.

**Fig. 4 fig4:**
[figure not shown]
The illustration of the Epee fencing-specific test setting.

### Data collection and management

2.10

The descriptive data, including participants' demographic information such as age, height, weight, and body mass index, self-reported injury history (i.e., injury site, time, stoppage period), current physical and mental health state, athletic level with training experience [25] (i.e., weekly training frequency, training years, highest competition level), coffee/smoking/sleep/diet behaviors (i.e., daily amount), educational status, academic courses and examination schedules in the upcoming study month, and currently registered competitions, will first be collected by an online questionnaire during familiarization.

All other quantitative outcome measures (i.e., subjective perceptions, performance variables, and HRmean) will be administered at two conditions, defined as EXP/CON_T0/1/2_. After data collection, participants' personal information will be completely deleted, except for the assigned exclusive identifier code (ID) to ensure pseudonymization. Data will be securely stored and confidentially managed according to the General Data Protection Regulation (GDPR) of 27 April 2016. The data collection and analysis will be monitored by the main investigator's three supervisors. The supervision group will make the final decision to terminate the study, if needed.

